#### 2.7.1. Primary Outcome

The primary outcome was the self-reported seven-day point prevalence of complete smoking abstinence (“not even a puff”) at 12-months follow-up. 

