### 2.11. Statistical Analysis

A descriptive analysis to summarize the characteristics of the total sample will be conducted. Comparisons between the two groups will be performed using an independent sample *t*-test for continuous variables (i.e., number of cigarettes smoked per day) and a chi-squared test for categorical variables (i.e., smoking status). Logistic regression analyses adjusted for baseline characteristics (i.e., sex, age, education level) will be carried out to examine whether abstinence rates differ significantly between conditions at the end of treatment, and at 3-, 6-, and 12-months follow-up. Mediation analysis will be conducted to analyze the role of different variables (i.e., depressive symptoms) in the relationship between treatment condition and smoking status. Multilevel and survival analysis will also be carried out to examine the relapse process. All data analysis will follow the intention-to-treat principle, which includes in the primary analysis all randomized participants [45]. A *p* value < 0.05 will be considered statistically significant.

The study results will be reported following the Consolidated Standards of Reporting Randomized Trials of Social and Psychological Interventions (CONSORT-SPI 2018) statements [46,47].

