Smoker (never quit during phase 1)	Smoking cessation tips Smoking self-monitoring tool Possibility of setting a quit date in a calendar Access to the intervention written materials in pdf format Self-recorded motivational videos List of reasons to quit tool Motivational strategies to quit Cognitive and behavioral strategies for coping with cravings Motivational notifications during the follow-up period promoting the initiation of a quit attempt	Smoking self-monitoring tool Access to the written materials in pdf format
Relapser (quit at least 24 h during phase 1)	Smoking cessation tips Smoking self-monitoring tool Possibility of setting a new quit date in a calendar Access to the intervention written materials in pdf format Self-recorded motivational videos List of reasons to quit tool Motivational strategies to initiate a new quit attempt Cognitive and behavioral strategies for coping with cravings Motivational notifications during the follow-up period promoting the initiation of a new quit attempt	Smoking self-monitoring tool Access to the written materials in pdf format

**Table 3 ijerph-19-09770-t003:** Timeline for data collection across the trial.

Measures	Measurement Time-Point				
	Baseline	End of Treatment	3-Months Follow-Up	6-Months Follow-Up	12-Months Follow-Up
Smoking Habit Questionnaire	X				
TUS Tobacco DSM-5 criteria	X				
FTCD	X	X	X	X	X
NDSS	X	X	X	X	X
MNWS	X	X	X	X	X
SSE	X	X	X	X	X
QSU	X	X	X	X	X
BDI-II	X	X	X	X	X
EQ-5D	X	X	X	X	X
APP-Q	X				
CSQ-8		X			
Satisfaction with App questionnaire		X	X	X	X
Follow-up questionnaire			X	X	X

TUS = Tobacco Use Disorder; FTCD = Fagerström Test of Cigarette Dependence; NDSS = Nicotine Dependence Syndrome Scale; MNWS = Minnesota Nicotine Withdrawal Scale; SSE = Self-Efficacy/Smoking Temptation Scale; QSU = Questionnaire of Urgency to Smoke; BDI-II = Beck Depression Inventory II; EQ-5D = EuroQoL-5D Quality of Life Questionnaire; APP-Q = Apps and Smartphone use Questionnaire; CSQ-8 = Client Satisfaction Questionnaire.

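### The adjusted logistic model for 12-month abstinence names only demographic covariates, although baseline dependence and cigarettes per day are collected from everyone

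*Protocol article*

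**What the plan says.** Section 2.7.1 sets the primary outcome as the "self-reported seven-day point prevalence of complete smoking abstinence" at 12 months, a binary outcome.

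Section 2.11 describes two kinds of comparison that could reach it. The first assigns methods by type of variable: a t-test for continuous variables and "a chi-squared test for categorical variables (i.e., smoking status"). The second is specific: "Logistic regression analyses adjusted for baseline characteristics (i.e., sex, age, education level) will be carried out", with the purpose "to examine whether abstinence rates differ significantly between conditions at the end of treatment, and at 3-, 6-, and 12-months follow-up".

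The section mentions a primary analysis once, to give its population: the intention-to-treat principle "includes in the primary analysis all randomized participants". No test is attached to that phrase. One significance rule covers everything: a p "value < 0.05 will be considered statistically significant".

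Section 2.6 and Table 3 show what is measured at baseline. Table 3 lists the "Fagerström Test of Cigarette Dependence" (FTCD), the NDSS and the BDI-II at baseline and at every later visit. Cigarettes per day comes from the Smoking Habit Questionnaire, given at baseline only. Inclusion criterion 4 in Section 2.3 requires all pre-treatment questionnaires to be filled out correctly before entry.

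**The concern.** Covariate adjustment in a randomised trial earns its place through covariates that predict the outcome. For smoking abstinence, the baseline measures closest to the outcome are dependence and consumption. The article collects both, with completeness guaranteed by an entry criterion, yet the covariates it names are sex, age and education level. If the named list is the model, some precision is given up although the data to gain it are in hand, and a chance imbalance in dependence between arms goes unadjusted. If the list is only illustrative, the covariates of the main model are not fixed and could be settled after the data are seen.

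A smaller matter goes with it. Everyone smokes at entry (at least six cigarettes per day under Section 2.3), so smoking status cannot differ between arms at baseline. A between-arm chi-squared test on it must use follow-up data. The article does not say that this test is subordinate to the logistic model.

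**Working it through.** **1. Inputs from the article.** Abstinence of 50% against 30%, 90% power, alpha 0.05 with sidedness not stated, 99 per arm, 25% attrition, 132 per arm and 264 in total (Section 2.3). Allocation is 1:1.

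**2. The plan's own figure.** With a one-sided alpha and unpooled variance, n = (1.645 + 1.282)² × (0.50×0.50 + 0.30×0.70) / 0.20² = 98.5, so 99 per arm. Then 99 / (1 − 0.25) = 132 per arm and 264 in total. The stated size reproduces as an unadjusted comparison of two proportions. With a two-sided 0.05 the same formula gives 120.8, so 121 (124 with pooled variance), and 99 per arm has 82.4% power. That is why the starting power below is 82-83% and not 90%. Sidedness is a separate question and is not pursued here.

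**3. Simulation.** The article does not say how strongly any baseline measure predicts abstinence, so a range was assumed. Each scenario has 5,000 trials and tests at two-sided 0.05. Demographics are represented by one prognostic score plus two unrelated covariates, and dependence with consumption by one further score. Assumed log odds ratios per SD, demographics then dependence:
- A: 0.2 and 0.3 (odds ratios 1.22 and 1.35)
- B: 0.2 and 0.5 (1.22 and 1.65)
- C: 0.3 and 0.8 (1.35 and 2.23)

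Power, 50% against 30%, 99 per arm:

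| Scenario | Chi-squared | Logistic, demographics | Logistic, plus dependence | Gain over demographics |
|---|---|---|---|---|
| A | 83.0% | 83.1% | 83.7% | 0.6 points |
| B | 82.0% | 81.9% | 83.8% | 1.8 points |
| C | 82.2% | 82.4% | 86.7% | 4.4 points |

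For a smaller effect, 45% against 30% at 132 per arm, adding dependence moves power from 71.7% to 72.2% (A), 71.2% to 73.7% (B) and 72.2% to 77.2% (C).

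Type I error, 30% in both arms, 132 per arm:

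| Scenario | Chi-squared alone | Demographics model alone | Either of these two | The two disagree |
|---|---|---|---|---|
| A | 5.1% | 4.9% | 5.6% | 1.3% |
| B | 5.0% | 5.1% | 5.6% | 1.0% |
| C | 5.2% | 5.0% | 6.0% | 1.8% |

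If the choice lies between the chi-squared test and a model that also carries dependence, the either-test rate is 5.9%, 6.1% and 6.9%.

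**4. Simulation error.** The standard error is about √(0.83×0.17/5000) = 0.5 points for power and √(0.05×0.95/5000) = 0.3 points for type I error. The gain in A is therefore close to nothing, while the gain in C is clear.

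**The case against.** The strongest objection is that nothing is excluded. The article uses its bracketed lists loosely. In the same section, one example stands for all continuous variables, and depressive symptoms alone illustrates a plural set of mediators. Sex, age and education level may likewise illustrate baseline characteristics in general, and the full covariate list is ordinary content for an analysis plan that is not shown. This stands in part: it would be wrong to say that the trial has decided against adjusting for dependence. But the article does name covariates, and every one it names is demographic.

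A reader might also infer that the primary outcome has two rival tests with neither deciding. The text does not support that. Only the logistic regression is given an efficacy purpose at 12 months. The chi-squared sentence is generic and names neither the primary outcome nor a time point, and Section 2.4.1 and Table 2 use smoking status for three follow-up categories. The logistic model is the likelier primary test; what is lacking is the label.

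A reader might go further and object that an odds ratio cannot express the 20-point difference used for sizing. Sizing on two proportions and testing the same null hypothesis by logistic regression is usual practice and contradicts nothing in Section 2.3. The choice of effect measure is a reporting preference.

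Finally, one might express the gain as participants saved. If 5%-10% of the outcome variation were explained, 264/0.95 − 264 = 14 and 264/0.90 − 264 = 29. That percentage is a pure assumption, and the formula belongs to linear models, so no weight is placed on it.

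**Conclusion.** The point holds as a modest improvement, not as an error that threatens the result. The model that carries the 12-month comparison names only demographic covariates, while FTCD, NDSS and cigarettes per day are available from every participant. Leaving them out of a randomised comparison costs precision, not validity.

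Adding a dependence and consumption score takes power from about 82-83% to 84-87% at 99 per arm. The upper end needs an odds ratio of about 2.2 per SD; at 1.35 per SD the gain is about half a point. Labelling the primary test removes an inflation of roughly 0.6 to 1.0 points above the nominal 5%, and up to about 2 points if the covariate list is also left open.

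These figures rest on covariate effects that the article does not give, a two-sided 0.05 that it does not state, and a single score standing in for two measures. That dependence and consumption predict abstinence better than demographics is likely, but it is also an assumption here.

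**What to change.** State in Section 2.11, or in the analysis plan before outcome data are examined, that:
- the primary test is the logistic regression for seven-day point-prevalence abstinence at 12 months;
- its covariates are sex, age, education level, baseline FTCD and baseline cigarettes per day, and no others;
- any chi-squared test on smoking status is supportive.

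A standardised risk difference with its 95% confidence interval beside the odds ratio is optional; it would put the result on the scale used for sizing.

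The cost is one or two sentences and two further model parameters. No new data are needed, and with inclusion criterion 4 in force no participant should be lost to a missing baseline covariate.

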## 3. Discussion

The present study will assess whether adding an App to a cognitive–behavioural smoking cessation treatment will improve short- and long-term abstinence rates, and reduce relapse rates in a sample of treatment-seeking smokers using a randomized clinical trial. The experimental condition will be provided with an App with therapeutic components (i.e., motivational strategies, craving management tools) along with the intervention and during a one-year follow-up period. The control group will receive the same smoking cessation treatment along with a control App in which participants are provided with a set of pdf documents that expand on the topics addressed in each session and a smoking self-monitoring tool. Adding an App with active cognitive–behavioral components to support the quitting process to a face-to-face intervention and throughout a year follow-up is innovative and might result in greater abstinence rates and lower relapse rates. We hypothesize that using this App would increase treatment intensity and accessibility to psychological strategies to quit, supporting the participants’ smoking cessation process.

Nowadays, the frequent use of smartphones and Apps is part of most people’s daily lives, and this is a resource that is beginning to be used for interventions aimed to promote the health of patients. An App with active components used as a complement to a psychological treatment, such as the one mentioned above, would also gather information about task completion and the tools used [18], providing relevant information about the adherence to the intervention.

Interventions for smoking cessation should pay special attention to relapse prevention, as relapse is a barrier to any treatment that targets addictive behaviors, and one of the main reasons for reduced overall success rates [48,49]. One of the strengths of the present project is that the experimental App specifically targets relapse prevention in abstinent patients, and relapse management in Phase 2 during the 12 months after the last treatment session, a period of time when relapse is most likely to occur. Thus, the goal of this Phase 2 of the experimental App will be relapse prevention in a critical time period where most relapses occur [12].

Some potential limitations should be acknowledged. As noted earlier, due to the COVID-19 pandemic and resource limitations, abstinence will only be self-reported, and biochemical verification will not be performed. The biochemical verification of abstinence is desirable, as it increases scientific rigor, limiting the impact of misreporting smoking status [50]. However, the current circumstances limit the benefits of biochemical verification due to participant and staff safety, economic costs, and sample collection feasibility. Moreover, the use of video calls instead of in-person sessions might impact trial outcomes. Video calls attended at home might be perceived by some patients as being intrusive; moreover, minorities, lower-income, and older populations might have more difficulties to access virtual treatment [51]. Similar limitations may be encountered in regard to the characteristics of the users of mHealth Apps [52]. However, the strengths, such as cost-effectiveness, ease to deliver at a large scale, accessibility, and attractiveness [24], clearly overpower these limitations.

## 4. Conclusions

We expect that adding a smartphone App to a well-established behavioral smoking cessation treatment will improve smoking cessation outcomes at the end of treatment and will reduce relapse rates at follow-ups. These findings will have important clinical implications, potentially transforming the way that people interact with health-care services. Any public health effort that targets smoking cessation is essential to improve people’s health and quality of life, and to reduce public health-care expenditure.

## Figures and Tables

**Figure 1 ijerph-19-09770-f001:**
[figure not shown]
Consort Diagram of Trial Progression.

**Figure 2 ijerph-19-09770-f002:**
[figure not shown]
SinHumo App features during phase 1.

**Figure 3 ijerph-19-09770-f003:**
[figure not shown]
SinHumo App features during phase 2 for abstainers.

**Figure 4 ijerph-19-09770-f004:**
[figure not shown]
Motivational notifications samples during phase 2 for relapsers (on the **left**) and smokers (on the **right**) of the SinHumo App.

**Figure 5 ijerph-19-09770-f005:**
[figure not shown]
SinHumo App features during phase 2 for relapsers and smokers.

**Table 1 ijerph-19-09770-t001:** Summary of session-by-session outline of intervention procedures and App components (Phase 1) in the experimental and control conditions.

	Experimental Condition (SinHumo App)	Control Condition (Control App)
Session1	Overview of treatment and App usage Smoking cessation treatment rationale Review cigarette self-monitoring using the App (tracking cigarettes smoked, pleasure experienced, and smoking antecedents and consequences) Automatically generated cigarettes consumption graph available in the App Discussion of reasons for smoking and for quitting and completion tool available in the App named “reasons to quit” Discussion about smoking history and past quit experiences Explanation of written materials included in the App about tobacco, nicotine dependence, smoking health consequences, and cessation benefits Explain nicotine fading through brand change and set weekly cigarette reduction goals using the App tool Intersession activities: - Brand change - Communicate to at least one person (family, friend, coworker, etc.) that he/she is trying to quit smoking in the next 30 days - Not smoking more cigarettes than the average of those smoked the previous week - Leave a third of the cigarette without smoking - Refuse cigarette offers Intersession motivational notification through the App	Overview of treatment Smoking cessation treatment rationale Review cigarette self-monitoring using the App (tracking cigarettes smoked, pleasure experienced, and smoking antecedents and consequences) Discussion of reasons for smoking and for quitting Discussion about smoking history and past quit experiences Explanation of written materials included in the App about tobacco, nicotine dependence, smoking health consequences, and cessation benefits Explain nicotine fading through brand change Intersession activities: - Brand change - Communicate to at least one person (family, friend, coworker, etc.) that he/she is trying to quit smoking in the next 30 days - Not smoking more cigarettes than the average of those smoked the previous week - Leave a third of the cigarette without smoking - Refuse cigarette offers
Session 2	Check homework and nicotine fading compliance Continue smoking self-monitoring through the App and analyze smoking behavior during the week Automatically generated cigarettes consumption graph available in the App Discuss brand change difficulties New brand change and reduction of number of cigarettes to smoke the next week, setting the cigarette reduction goal using the App tool Review importance of social support Introduce stimulus control technique to remove situations conditioned to smoking using the App Nicotine withdrawal and strategies to avoid it Breathing exercises and relaxation techniques (practice as homework using the videos available in the App) Intersession motivational notification through the App Reinforcement notification of goal achievement through the App	Check homework and nicotine fading compliance Continue smoking self-monitoring through the App and analyze smoking behavior during the week Discuss brand change difficulties New brand change and reduction of number of cigarettes to smoke the next week Review importance of social support Introduce stimulus control technique to remove situations conditioned to smoking Nicotine withdrawal and strategies to avoid it Breathing exercises and relaxation techniques (practice such as homework)
Intervention Session 3	Check nicotine fading, cigarette reduction, and stimulus control compliance Check breathing exercises compliance and strategies to avoid withdrawal symptoms Continue cigarette self-monitoring through the App and analyze smoking behavior Automatically generated cigarettes consumption graph available in the App New brand change and reduce number of cigarettes to smoke the next week setting the cigarette reduction goal using the App tool Continue stimulus control technique using the App Explain written materials for weight control and exercise available in the App Continue with breathing exercises compliance and strategies to avoid withdrawal symptoms Rationale of mood influence in smoking cessation (written materials available in the App) Homework: daily activities self-monitoring using App tool Intersession motivational notification through the App Reinforcement notification of goal achievement through the App	Check nicotine fading, cigarette reduction, and stimulus control compliance Check breathing exercises compliance and strategies to avoid withdrawal symptoms Continue cigarette self-monitoring through the App and analyze smoking behavior New brand change and reduce number of cigarettes to smoke the next week Continue stimulus control technique Explain written materials for weight control and exercise available in the App Continue with breathing exercises compliance and strategies to avoid withdrawal symptoms Rationale of mood influence in smoking cessation (written materials available in the App) Homework: daily activities self-monitoring
Session 4	Check nicotine fading, cigarette reduction, and stimulus control compliance Check breathing exercises compliance and strategies to avoid withdrawal symptoms Continue smoking self-monitoring through the App and analyze smoking behavior Automatically generated cigarettes consumption graph available in the App New brand change and reduction of number of cigarettes to smoke the next week, setting the cigarette reduction goal using the App tool Continue stimulus control technique using the App Stress and anxiety management strategies Check activity scheduling through the App and encourage recognizing patterns of depressed behavior and the way in which engaging in enjoyable and important activities may impact their overall mood Homework: continue activity scheduling through the App, create a pleasant activities list and choose one to do during the week Intersession motivational notification through the App Reinforcement notification of goal achievement through the App	Check nicotine fading, cigarette reduction, and stimulus control compliance Check breathing exercises compliance and strategies to avoid withdrawal symptoms Continue smoking self-monitoring through the App and analyze smoking behavior New brand change and reduction of number of cigarettes to smoke the next week Continue stimulus control technique Stress and anxiety management strategies Check activity scheduling, and encourage recognizing patterns of depressed behavior and the way in which engaging in enjoyable and important activities may impact their overall mood Homework: continue activity scheduling, create a pleasant activities list, and choose one to do during the week
Session 5	Check nicotine fading, cigarette reduction, and stimulus control compliance using the App Check activity scheduling, pleasant activities list elaboration, and pleasant activity compliance using the App tools Continue smoking self-monitoring through the App and analyze smoking behavior Automatically generated cigarettes consumption graph available in the App New brand change and reduction of number of cigarettes to smoke the next week, setting the cigarette reduction goal using the App tool Management of anxiety and anger Self-reinforcing Changing tobacco-related misconceptions Problem-solving training Recognize avoidance behavior and impact on mood Activity scheduling through the App and engagement in two pleasant activities during the week Intersession motivational notification through the App Reinforcement notification of goal achievement through the App	Check nicotine fading, cigarette reduction, and stimulus control compliance Check activity scheduling, pleasant activities list elaboration, and pleasant activity compliance Continue smoking self-monitoring through the App and analyze smoking behavior New brand change and reduction of number of cigarettes to smoke the next week Management of anxiety and anger Self-reinforcing Changing tobacco-related misconceptions Problem-solving training Recognize avoidance behavior and impact on mood Activity scheduling and engagement in two pleasant activities during the week
Session 6	Quitting experience and withdrawal symptoms Discuss and plan for high-risk lapse and relapse situations Motivating factors for maintaining abstinence Benefits of quitting smoking Common barriers for maintaining abstinence Ruminative thoughts, smoking cessation process, and relapse Check activity scheduling and pleasant activity compliance using the App Activity scheduling through the App for the next week and engagement in 2 pleasant activities/week Intersession motivational notification through the App Reinforcement notification of goal achievement through the App	Quitting experience and withdrawal symptoms Discuss and plan for high-risk lapse and relapse situations Motivating factors for maintaining abstinence Benefits of quitting smoking Common barriers for maintaining abstinence Ruminative thoughts, smoking cessation process, and relapse Check activity scheduling and pleasant activity compliance Activity scheduling for the next week and engagement in 2 pleasant activities/week
Session 7	Quitting experience and withdrawal symptoms Discuss and plan for high-risk lapse and relapse situations Motivating factors for maintaining abstinence Benefits of quitting smoking Review how behavioral activation impacts their overall mood Review avoidance behavior and ruminative thoughts’ significance Strategies for relapse prevention Intersession motivational notification through the App Reinforcement notification of goal achievement through the App	Quitting experience and withdrawal symptoms Discuss and plan for high-risk lapse and relapse situations Motivating factors for maintaining abstinence Benefits of quitting smoking Review how behavioral activation impacts their overall mood Review avoidance behavior and ruminative thoughts’ significance Strategies for relapse prevention
Session 8	Managing the future as ex-smokers Encouragement for abstinence maintenance Support for lapses and relapse Review motivating factors, lifestyle changes, physical and cognitive–behavioral health improvement Review behavioral activation strategies Treatment conclusion and management of potential obstacles Intersession motivational notification through the App Reinforcement notification of goal achievement through the App	Managing the future as ex-smokers Encouragement for abstinence maintenance Support for lapses and relapse Review motivating factors, lifestyle changes, physical and cognitive–behavioral health improvement Review behavioral activation strategies Treatment conclusion and management of potential obstacles

**Table 2 ijerph-19-09770-t002:** App components according to intervention conditions and smoking status during phase 2 (one-year follow-up).

Smoking Status	Experimental Condition (SinHumo App)	Control Condition (Control App)
Abstainer	Smoking self-monitoring tool (to use in case a lapse occurs) Access to the intervention written materials in pdf format Gains and achievements according to abstinence duration after the intervention (health benefits, saved money) Abstinence maintenance tips Self-recorded motivational videos List of reasons to quit to consult in case of experiencing tobacco craving Motivational strategies to maintain abstinence Cognitive and behavioral strategies for coping with cravings Motivational notifications during all the follow-up period	Smoking self-monitoring tool Access to the written materials in pdf format
Smoker (never quit during phase 1)	Smoking cessation tips Smoking self-monitoring tool Possibility of setting a quit date in a calendar Access to the intervention written materials in pdf format Self-recorded motivational videos List of reasons to quit tool Motivational strategies to quit Cognitive and behavioral strategies for coping with cravings Motivational notifications during the follow-up period promoting the initiation of a quit attempt	Smoking self-monitoring tool Access to the written materials in pdf format
Relapser (quit at least 24 h during phase 1)	Smoking cessation tips Smoking self-monitoring tool Possibility of setting a new quit date in a calendar Access to the intervention written materials in pdf format Self-recorded motivational videos List of reasons to quit tool Motivational strategies to initiate a new quit attempt Cognitive and behavioral strategies for coping with cravings Motivational notifications during the follow-up period promoting the initiation of a new quit attempt	Smoking self-monitoring tool Access to the written materials in pdf format

**Table 3 ijerph-19-09770-t003:** Timeline for data collection across the trial.

Measures	Measurement Time-Point				
	Baseline	End of Treatment	3-Months Follow-Up	6-Months Follow-Up	12-Months Follow-Up
Smoking Habit Questionnaire	X				
TUS Tobacco DSM-5 criteria	X				
FTCD	X	X	X	X	X
NDSS	X	X	X	X	X
MNWS	X	X	X	X	X
SSE	X	X	X	X	X
QSU	X	X	X	X	X
BDI-II	X	X	X	X	X
EQ-5D	X	X	X	X	X
APP-Q	X				
CSQ-8		X			
Satisfaction with App questionnaire		X	X	X	X
Follow-up questionnaire			X	X	X

TUS = Tobacco Use Disorder; FTCD = Fagerström Test of Cigarette Dependence; NDSS = Nicotine Dependence Syndrome Scale; MNWS = Minnesota Nicotine Withdrawal Scale; SSE = Self-Efficacy/Smoking Temptation Scale; QSU = Questionnaire of Urgency to Smoke; BDI-II = Beck Depression Inventory II; EQ-5D = EuroQoL-5D Quality of Life Questionnaire; APP-Q = Apps and Smartphone use Questionnaire; CSQ-8 = Client Satisfaction Questionnaire.

